## Abstract

**Background:**

Each year, millions of Americans sustain acquired brain injuries (ABI) which result in functional impairments, such as poor balance and autonomic nervous system (ANS) dysfunction. Although significant time and energy are dedicated to reducing functional impairment in acute phase of ABI, many individuals with chronic ABI have residual impairments that increase fall risk, decrease quality of life, and increase mortality. In previous work, we have found that yoga can improve balance in adults with chronic (i.e., ≥6 months post-injury) ABI. Moreover, yoga has been shown to improve ANS and brain function in healthy adults. Thus, adults with chronic ABI may show similar outcomes. This protocol details the methods used to examine the effects of a group yoga program, as compared to a group low-impact exercise, on primary and secondary outcomes in adults with chronic ABI.

**Methods:**

This study is a single-blind randomized controlled trial comparing group yoga to group low-impact exercise. Participants must be ≥18 years old with chronic ABI and moderate balance impairments. Group yoga and group exercise sessions occur twice a week for 1 h for 8 weeks. Sessions are led by trained adaptive exercise specialists. Primary outcomes are balance and ANS function. Secondary outcomes are brain function and structure, cognition, quality of life, and qualitative experiences. Data analysis for primary and most secondary outcomes will be completed with mixed effect statistical methods to evaluate the within-subject factor of time (i.e., pre vs. post intervention), the between-subject factor of group (yoga vs. low-impact exercise), and interaction effects. Deductive and inductive techniques will be used to analyze qualitative data.

**Discussion:**

Due to its accessibility and holistic nature, yoga has significant potential for improving balance and ANS function, along with other capacities, in adults with chronic ABI. Because there are also known benefits of exercise and group interaction, this study compares yoga to a similar, group exercise intervention to explore if yoga has a unique benefit for adults with chronic ABI.

**Clinical trial registration:**ClinicalTrials.gov, NCT05793827. Registered on March 31, 2023.

## Introduction

1

Each year, an estimated 2.9 million Americans sustain acquired brain injuries (ABI) that result in emergency department visits, hospitalizations, and death (Schiller et al., 2012). ABI is an umbrella term that includes traumatic brain injuries (TBI) and non-traumatic injuries, including stroke, anoxic injuries, brain tumors, and other conditions that damage brain tissue. Although there are many treatment strategies in the early weeks and months after ABI, millions of individuals live with residual disability (Rutherford and Corrigan, 2009; Corrigan and Hammond, 2013; Whiteneck et al., 2016). This residual, chronic disability often includes significant impairments across multiple functional domains (e.g., motor, cognitive, emotional) and decreased brain function (Wilson et al., 2017). Two prominent and interconnected impairments – poor balance (McCulloch et al., 2010; Perez et al., 2018; Klima et al., 2019) and autonomic nervous system (ANS) dysfunction (Khalid et al., 2019; Xiong and Leung, 2019) – can together *and* independently increase fall risk, decrease quality of life, and increase mortality.

To date, there are few options for addressing impairments in adults with chronic ABI. However, community-based and holistic interventions, like hatha yoga, may be highly effective for simultaneously addressing balance (Green et al., 2019), ANS dysfunction (Zou et al., 2018) and may even improve brain function (Gothe et al., 2019). Hatha yoga includes breathwork, stretching, holding of postures, and meditation. Because stretching and holding postures requires *and* challenges balance, it is unsurprising that yoga interventions often elicit improvements in balance performance (Schmid et al., 2012; Stephens et al., 2020). Likewise, the breathwork and meditation components of hatha yoga may support improved ANS function, particularly for individuals with ABI. Briefly, ANS dysfunction following ABI is typically characterized by hyper-activation of the sympathetic nervous system, which can have damaging or even fatal impact on internal organs (Henden et al., 2014). It is theorized that the use of breathwork in hatha yoga may stabilize sympathetic and parasympathetic nervous system activity (Zou et al., 2018), but this has not yet been established for adults with ABI. Similarly, research with healthy adults has found that yoga can improve brain function (Gothe et al., 2019), but this has also not been tested in adults with chronic ABI. We theorize that yoga-induced improvements in functional abilities, like balance, are likely supported by improvements in brain structure and function.

Our research team has conducted two yoga feasibility studies with adults with chronic ABI to establish that our recruitment, retention, intervention, and assessment procedures (which includes neuroimaging methods) are feasible (Stephens et al., 2020, 2023). Notably, in these studies and other studies conducted by our team, we have seen that 8-weeks of yoga can improve balance and mobility (Stephens et al., 2020), cognition (Grieb et al., in press) and quality of life (Grimm et al., 2017). We have also have replicated that 8-weeks of yoga can improve balance in adults with chronic ABI, and we found preliminary evidence of improved brain function, even in the absence of measurable balance improvement (Stephens et al., 2023). Further, participants with chronic ABI have qualitatively shared that yoga improved a myriad of functional capacities (e.g., eating and swallowing, functional mobility, caring for pets, etc., Weaver et al., in press). Thus, our prior work suggests that yoga can support improvements across multiple functional domains. Still, the primary outcomes of interest for our current study are balance and ANS function, as they are the most logical areas of improvement given the components of hatha yoga (i.e., stretching/holding of postures and breathwork and meditation). Secondary outcomes include those that likely underpin functional improvements (i.e., changes in brain structure and function) and previously observed outcomes (i.e., cognition, quality of life, and qualitative experiences).

Specifically, our team is now conducting a single-blind pilot randomized control trial comparing two intervention arms: 8-weeks of group yoga and 8-weeks of low-impact group exercise in adults with chronic acquired brain injury. All prior studies (Grimm et al., 2017; Stephens et al., 2020, 2023) have been conducted as single-arm yoga intervention studies where participants served as their own controls, and baseline assessments were conducted before no-contact waiting periods and/or the intervention. Therefore, it is possible that the positive outcomes we have reported could be exclusively attributed to well-established benefits of physical exercise or social interaction. In order to determine if yoga has a distinctive impact on functional outcomes, like balance and ANS function, it is necessary to include a control group that mirrors many of the features of the yoga intervention, but lacks unique features of yoga (e.g., breath-to-movement connection). Thus, adding a low-impact group exercise control (Leach et al., 2023) is an essential next step to evaluate if yoga has a unique benefit for adults with chronic ABI. Again, our primary outcome measures are designed to evaluate balance performance and heart rate variability (HRV), as an indicator of ANS function. Secondary outcome measures are designed to: (1) measure neural underpinnings of functional improvements, specifically - functional and structural connectivity of neural networks and task-dependent neural activation during balance tasks and (2) evaluate previously observed outcomes of cognition, quality of life, and qualitative experiences. The overarching purpose of this manuscript is to describe, in detail, all components of our trial protocol to support transparency and replication of methods.

## Methods and analysis

2

### Study design and ethics

2.1

This study is being conducted within university laboratories and buildings for pre-and post-intervention assessments and interventions. All procedures are completed at a single site in the Mountain West subregion of the United States of America and described using SPIRIT reporting guidelines and checklist (Chan et al., 2013). The study consists of two participant cohorts: Cohort 1 and Cohort 2. A cohort design was selected to ensure small class sizes during yoga and control exercise sessions to support participant engagement, success, and safety. All study procedures for Cohort 1 and Cohort 2 are identical and the timeline of study components for both cohorts is depicted in Figure 1.

**Figure 1 fig1:**
[figure not shown]
SPIRIT figure of study components. Timeline of enrollment, interventions, and assessments for participants in Cohort 1 and Cohort 2. The baseline time point is pre-intervention, and the close-out time point is post-intervention.

### Selection of subjects

2.2

Participants are included if they are at least 18 years old, have sustained an ABI at least 6 months before start of study (operationally defined by our team as “chronic”), and have a self-reported balance impairment of moderate or greater, via the Neurobehavioral Symptom Inventory balance item (King et al., 2012). If completing magnetic resonance imaging (MRI) assessments, participants must meet standard screening criteria for a 3 Tesla scanner. To support successful recruitment, participants are not required to be yoga or exercise naïve, as the research was conducted in a relatively small community. Participants are excluded if they have not sustained an acquired brain injury or if they sustained an acquired brain injury within the past 6 months. They are also excluded if they self-report a mild balance impairment or no balance impairment, again via the neurobehavioral symptom inventory (King et al., 2012). The interventionists leading the yoga and low-impact exercise sessions were required to be a certified yoga instructor or personal trainer, respectively. Both interventionists had to be willing to follow a standardized protocol, designed by the co-principal investigators (Co-PIs), and complete human subjects training. Additionally, both interventionists were trained by occupational therapists on appropriate ways to communicate with and physically support individuals with brain injury during yoga and exercise.

### Recruitment

2.3

Recruitment is ongoing and includes direct communication with local brain injury providers (e.g., physicians, occupational and physical therapists, etc.) and community organizations (e.g., Brain Injury Association of Colorado) to share information about the study via member list serves, quarterly newsletters, and support groups. Additionally, physical flyers have been posted and distributed within the local community and at the university, and radio and newspaper advertisements were used to expand reach.

### Participant retention

2.4

To support participant retention, during eligibility screening, participants are fully informed of all study components and when each will occur. This is done to prevent loss of data and/or attrition due to known conflicts. Additionally, participants are sent reminders (via text message) for all study appointments, including pre-intervention assessment visits, yoga/exercise class sessions, and post-intervention assessment visits. To further support retention, attendance is taken at each class session, and participants are contacted if they miss a session and their reason for missing is recorded. Additionally, participant incentives are provided at the end of the last yoga/exercise class. Incentives are study materials – exercise mats, smart watches, and chest straps – that are used for each session and retained by the study team, so they are not lost or forgotten for sessions. Post-intervention assessment visits will be completed for all participants who participate in yoga/exercise sessions, but attendance data will be used to interpret post-intervention data, particularly for participants who miss multiple sessions.

### Sample size

2.5

Power was determined by focusing on the primary outcome of balance. Thus, using balance data from our first feasibility study (Stephens et al., 2020), a power analysis was completed in G Power (version 3.118) (Faul et al., 2007) using a matched pairs t-test with a medium effect size (*d* = 0.5), a minimum power of 0.8 and a significance level of 0.05 to determine that 17 participants per group are needed (*n* = 34). We planned to enroll 48 participants due to potential attrition or enrollment challenges. Limited enrollment was achieved for Cohort 1 so planned enrollment is now 36 participants which still meets the minimum power to detect a medium effect size.

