#### Primary outcomes

4.1.1

Given our prior work (Schmid et al., 2012; Stephens et al., 2020), we expect significant improvements in balance as a result of the yoga intervention. However, we also expect that participants in the low-impact exercise group will experience improvements in balance. As such, we hypothesize significant within-subject differences in balance performance, but no between-group differences. We have different predictions for the ANS outcome. To-date, there is limited research investigating the effects of yoga on ANS function in populations with chronic acquired brain injury. Nevertheless, evidence from healthy adults indicate that yoga may improve ANS function (Zou et al., 2018). As such, we hypothesize that participants in the yoga group will have significantly greater improvements in ANS function than those in the low-impact experience group.

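### The 17 per group in section 2.5 is half of a one-group paired requirement, so 0.8 power holds for the pre/post change pooled over both arms, not per arm or between arms

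*Protocol article*

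**What the plan says.** Section 2.5 (Sample size) says that power was set on balance, one of the primary outcomes, "using a matched pairs t-test with a medium effect size" of d = 0.5. It gives "a minimum power of 0.8 and a significance level of 0.05 to determine that 17 participants per group are needed", for a total of 34. The first enrolment target was 48. After low recruitment to Cohort 1, "planned enrollment is now 36 participants which still meets the minimum power to detect a medium effect size".

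The trial has two parallel arms, and section 2.6 allocates six and six in Cohort 1. Section 2.13 plans mixed effects models with time and group for balance and for LF band power, and the abstract adds the interaction. Section 4.1.1 (Expected results, Primary outcomes) sets a different hypothesis for each primary outcome. For balance it expects change within subjects and no difference between groups. For autonomic function it expects that "participants in the yoga group will have significantly greater improvements in ANS function" than the exercise group. Section 1 says the control arm was added to learn whether yoga has a benefit beyond exercise and social contact.

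**The concern.** A matched pairs t-test has one group, and its sample size is the number of pairs in that group. A two-arm trial that quotes such a test and then gives a number per group has either computed a requirement for each arm or divided a one-group total by two. In the second case neither arm has the stated power, and the stated power does not describe the randomised comparison.

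What is at stake is how the results will be read. The control arm exists for the between-arm question, and one of the two primary hypotheses is a between-arm difference. If power for that comparison is well below 0.8, a non-significant difference is likely even when a medium one exists. It could then be taken as evidence that yoga adds nothing. For balance it would appear to confirm the predicted absence of a group difference.

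**Working it through.** **Inputs from section 2.5:** matched pairs t-test; d = 0.5; power 0.8; alpha 0.05; 17 per group, 34 in total; revised enrolment 36, which is 18 per arm at 1:1. The section does not say whether the test is one- or two-sided, and it gives no SD and no pre/post correlation.

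**1. The plan's own figure.** For n pairs, df = n − 1 and the noncentrality is d√n, with d in units of the SD of change.
- n = 34: 0.5 × √34 = 2.92, critical t (33 df) 2.03, power 0.808.
- n = 33: power 0.795.

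So 34 pairs is the smallest two-sided n, and it equals the plan's total exactly. One-sided, the smallest n is 27. Normal approximations give 32 (two-sided) and 25 (one-sided). A two-sample test gives 64 per arm (two-sided) or 51 (one-sided). None of these returns 17, but 34 / 2 does.

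**2. Pooled pre/post change.** Power is 0.81 with 34 pairs and 0.83 with 36. The margin is 36 − 34 = 2 participants. Section 2.15 removes missing data without imputation, so completers are what count.

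**3. Pre/post change within one arm, d = 0.5.**
- n = 17: 0.5 × √17 = 2.06, critical t (16 df) 2.12, power 0.49.
- n = 18: 0.5 × √18 = 2.12, critical t (17 df) 2.11, power 0.52.

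Power of 0.8 within one arm needs 34 in that arm.

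**4. Between-arm difference in change, d = 0.5 SD of change.** With n per arm, df = 2n − 2 and the noncentrality is d√(n/2).
- n = 17: 0.5 × √8.5 = 1.46, critical t (32 df) 2.04, power 0.29.
- n = 18: 0.5 × √9 = 1.50, critical t (34 df) 2.03, power 0.31.

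Power of 0.8 needs 64 per arm. The difference detectable with power 0.8 is 0.99 SD of change at 17 per arm and 0.96 at 18.

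**5. Sensitivity: d in raw-score SD, baseline-adjusted comparison.** With pre/post correlation ρ, the residual SD is √(1 − ρ²) of the raw SD, so the effective d is 0.5 / √(1 − ρ²). The document gives no ρ; the range 0.5 to 0.8 is an assumption.

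| ρ (assumed) | effective d | power, 17 per arm | detectable raw-score d at power 0.8, 17 per arm |
|---|---|---|---|
| 0.5 | 0.5 / 0.866 = 0.577 | 0.37 | 0.86 |
| 0.8 | 0.5 / 0.600 = 0.833 | 0.65 | 0.60 |

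**The case against.** The strongest reply is that the total was built for balance, and the balance hypothesis is a within-subject change with no group difference. A pre/post test on all participants is close to that hypothesis, and its power is 0.81 at 34 and 0.83 at 36. This stands: the total is not wrong for that purpose, and the sentence about 36 is true of the pooled test. It does not rescue the per-group wording, since each group alone has power of about 0.5. Nor does the pooled test use the randomised comparison.

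A second reply is that 17 per arm could be genuine if d = 0.5 is in raw-score SD and ρ is high. Within an arm, 17 pairs reach about 0.8 two-sided once ρ is roughly 0.76 or more. Nothing in section 2.5 says this, and the exact match at 34 points to a split total. Even then, between-arm power stays below 0.8 over the range in step 5.

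A third is that a 2 × 2 repeated-measures interaction with f = 0.25 and ρ = 0.5 also gives N = 34 (power 0.807). The plan names a different test, however. That f corresponds to a between-arm difference in change of about 1.0 SD, not 0.5.

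Finally, sections 1, 3.2 and 4 call this a pilot, and a pilot need not be powered for its between-arm question. That is fair, and it shapes the remedy. But this pilot states a formal power and between-arm hypotheses of significance, so what it says about power should be accurate.

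**Conclusion.** The point holds as a mislabelled requirement and a power statement without its limits. The stated 0.8 applies to one quantity: the pre/post balance change pooled over both arms, at d = 0.5 SD of change and two-sided 0.05. It does not apply within an arm (0.49 to 0.52). Nor does it apply to a between-arm difference in change of the same size (0.29 to 0.31, or 0.37 to 0.65 at 17 per arm under the baseline-adjusted assumptions).

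Three stronger readings are not supported:
- A reader might infer that the plan claims 80% power for yoga versus exercise. It does not. Section 2.5 names a paired test on balance and makes no between-arm claim, although the per-group wording invites the inference.
- A reader might treat the gap between 48 and 34 as a planned dropout rate and apply it to 36. The plan gives attrition and enrolment difficulty together as the reasons for 48 and states no dropout rate. Only the margin of two is established.
- A reader might count the lack of a calculation for autonomic function as a separate error. Section 2.5 says openly that sizing rests on balance. The consequence is only that the 0.8 cannot be carried over to that hypothesis.

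**What to change.** Keep enrolment at 36 and restate section 2.5 along these lines:

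> In total, 34 completers (both arms pooled) give 0.81 power for a pre/post change of d = 0.5 SD of change at two-sided alpha 0.05; enrolling 36 allows two losses. With 17 to 18 per arm, power for a change of d = 0.5 within one arm is about 0.5, and for a between-arm difference in change of d = 0.5 SD of change about 0.3. The between-arm difference detectable with 80% power is about 1.0 SD of change (about 0.6 to 0.9 raw-score SD with baseline adjustment, assuming a pre/post correlation of 0.8 to 0.5).

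Remove the per-group wording, and limit the sentence that 36 is sufficient to the pooled pre/post balance change. Add that between-arm results of this pilot are estimates reported with confidence intervals, and that a non-significant difference is not evidence that yoga has no unique benefit.

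The cost is wording only, with no extra participants and no change to design or analysis. The stated power becomes less favourable.

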### Random allocation of intervention arms

2.6

The study biostatistician created the allocation sequence. Up to twenty-four subjects for each cohort were randomly assigned to the yoga or exercise group. First, two blocks of 12 were created, and the randomization scheme was applied separately to each block. Within each block, 12 random numbers were generated using the pseudo-random number generating rand() function in Microsoft Excel. For the first cohort (where 12 individuals were recruited), six of those random numbers were associated with the yoga group and six were associated with the control group. The random number and associated group label were sorted from smallest random number to largest. The resulting randomization scheme was assigned to enrolled participants 001–012 such that six participants were randomly assigned to the yoga group and six participants were randomly assigned to the exercise group for the first cohort. The final allocation sequence was shared with the Co-PI and project manager, who is responsible for creating sealed envelopes that link participant IDs to group assignment. These steps will be repeated for the second cohort. Implementation of group assignment is completed in the following steps. First, the project manager or the PI screens participants for eligibility. Eligible participants are scheduled for a pre-intervention assessment visit where consenting, enrollment, and data acquisition are completed. Following consent, participants are given a unique participant ID number that is given in order of arrival to pre-intervention assessment visits. For example, the first person who arrives for a pre-intervention assessment is given a participant ID of 001. At the end of the pre-intervention visit, the project manager gives participants their sealed envelope, so they are aware of their group assignment.

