### Consent

3.3

Written informed consent is acquired by the study PI and Co-PI from participants or their legal power of attorney. This study includes two consent forms (see appendices) – one for the main study and one specific to MRI procedures (this is only acquired from participants who are eligible for MRI). Consent is acquired during a pre-intervention assessment visit, which occurs after participants are screened for eligibility. To note, if participants are deemed ineligible for the study during screening, the research team retains none of their information, with the exception of their initial email correspondence for recruitment tracking. Written informed consent procedures include the following steps: (1) Participants are emailed consent form(s) in advance of their pre-intervention assessment visit. (2) Upon arrival at the pre-intervention assessment visit, participants review a printed copy of the consent form(s) with the PI or Co-PI, who clarify procedures and answer questions. (3) After questions are addressed, participants initial and sign consent form(s) and the PI or Co-PI also signs the form(s). All participants are offered a copy of the signed consent form at this time. (4) Throughout the study, participants are reminded that they can decline to complete any procedures, which has no penalty except possible removal from the study.

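### The allocation sequence is given to two roles that also recruit (the Co-PI and the project manager), so concealment is open to breach by design

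*Protocol article*

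**What the plan says.** Section 2.6 (Random allocation of intervention arms) separates generation of the sequence from recruitment: "The study biostatistician created the allocation sequence". It then passes the result on: "The final allocation sequence was shared with the Co-PI and project manager, who is responsible for creating sealed envelopes".

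The same section describes recruitment. For screening, "the project manager or the PI screens participants for eligibility". Next, "Eligible participants are scheduled for a pre-intervention assessment visit where consenting, enrollment, and data acquisition are completed". After consent, each participant receives a "unique participant ID number that is given in order of arrival to pre-intervention assessment visits". The list is matched to those IDs in sequence, in blocks of 12 with six per arm. The project manager hands over the sealed envelope at the end of the visit. The section adds that the same steps will be used for the second cohort.

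Section 3.3 (Consent) says who takes consent: "Written informed consent is acquired by the study PI and Co-PI". Section 2.7 (Masking) describes the Co-PI as unmasked and the PI as masked until post-intervention assessments are completed and scored.

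**The concern.** Random generation protects the comparison only if the people who bring participants into the trial cannot foresee the next assignment. Here both named recipients of the sequence have a recruiting role. Someone who knows the next arm can, without intending to, press harder or less hard for consent, or bring a visit forward or put it back. The arms can then differ at entry in motivation, prior yoga or exercise experience (allowed under section 2.2), or expected attendance.

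The introduction says the exercise control was added because single-arm studies could not separate yoga from the general benefits of exercise and social contact. Section 4.1 predicts that yoga will be superior on autonomic function and on most secondary outcomes. Those claims rest on the between-arm comparison that concealment protects.

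**Working it through.** The plan states no figure to reproduce. The main check is to set the roles side by side.

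| Role | Named as receiving the sequence (2.6) | Recruiting task | Makes or hands over envelopes (2.6) | Masking (2.7) |
|---|---|---|---|---|
| Biostatistician | Creates it | None stated | No | Not stated |
| Project manager | Yes | Screens (2.6) | Both | Not stated by name |
| Co-PI | Yes | Takes consent (3.3) | No | Unmasked |
| PI | No | Screens (2.6) and takes consent (3.3) | No | Masked |

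Both list recipients (2 of 2) recruit. One of the two screeners and one of the two consent-takers hold the list. Sections 2.6, 2.7 and 3.3 describe no barrier between holding the list and doing those tasks.

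**Timing.** Consent comes first, then the ID, then baseline measurement, then the envelope. Because IDs run in arrival order, the arm for the next ID is already fixed on the list when the next person arrives to consent. Envelopes are handed over visit by visit, so assignments exist on paper while later participants may still be unconsented.

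**Foreknowledge in one block of 12 (six per arm).**

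- List holder: 12/12 = 100% of the arms attached to the IDs.
- No list, but each past assignment is learned, and the guess is always the arm with more places left. With *a* and *b* places left, the expected number of correct guesses is g(a,b) = max(a,b)/(a+b) + [a/(a+b)]·g(a−1,b) + [b/(a+b)]·g(a,b−1), with g(0,0) = 0. This gives g(6,6) = 7.716. The closed form agrees: 6 + 2^11/C(12,6) − 1/2 = 6 + 2048/924 − 0.5 = 7.716. As a share, 7.716/12 = 64.3%. On average 12/7 = 1.7 assignments at the end of a block are certain.
- No list, and past assignments hidden: 6/12 = 50%.

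Taking the list away from recruiting roles therefore lowers foreknowledge from 100% to 64% if assignments are still revealed one by one, and to 50% if they are not.

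**Detectability (illustration, assuming 36/2 = 18 per arm).** The standard error of a baseline difference between arms is SD × √(2/18) = 0.333 SD, so chance alone gives differences up to about 1.96 × 0.333 = 0.65 SD in either direction. A moderate imbalance caused by selection would not stand out from this.

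**Participants still to be protected.** Section 2.5 plans 36 and section 2.6 reports 12 recruited in Cohort 1: 36 − 12 = 24, or 24/36 = 67%.

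**The case against.** Several points on the other side have force.

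- The PI also screens and consents, is masked, and is not named as a list holder. For participants handled by the PI alone, the envelopes may conceal as intended. This stands: the exposure runs through two roles, not through every recruiter. A reader might infer that anyone who screens or books visits knows the next arm. The article does not support that, and it does not say who books visits.
- Knowing the arm for an ID is not the same as knowing a given person's arm at screening, because the ID is fixed only on arrival. This also stands. The 100% describes the list, and using it at screening would require predicting or steering visit order. It does not help at the consent step.
- Eligibility leaves little discretion (age, time since injury, a self-reported balance item), and Cohort 1 recruited 12 for up to 24 places, so there was little surplus to choose from. This makes selective screening less likely; encouragement to consent and visit order remain open.
- Primary outcomes are measured before the envelope is handed over, so baseline imbalance in balance or heart rate variability can be inspected. It would therefore be too strong to call selection undetectable, but the check is weak at this size and says nothing about unmeasured traits.
- The article does not say when the list was shared relative to screening. Even if it was shared late, visit-by-visit envelopes mean it existed while others could still be awaiting consent.
- The trial is a pilot with masked balance assessors. Masked assessment guards against biased measurement, not against biased entry.

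**Conclusion.** The point holds in a limited form. By stated procedure, two recruiting roles can know the arm attached to the next ID before that person consents, and the sealed envelopes do not guard against either of them. No other section repairs this.

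A reader might go further and conclude that Cohort 1 was unconcealed or that allocation was manipulated. The article supports neither: it shows an opening for a breach, not that one occurred.

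For a list holder, foreknowledge is complete at the level of the ID, against 64% or 50% without the list. Any resulting selection would be hard to detect or fully correct in about 36 participants. The conclusion assumes that section 2.6 was followed as written and that no unreported barrier separated the list from recruiting. It should be acted on before further participants are allocated.

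**What to change.** For Cohort 2, if its enrolment is not complete (section 2.3 says recruitment is ongoing, section 2.8 places the cohort in fall 2023, and current status is not shown):

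1. The biostatistician keeps the sequence. The Co-PI and project manager see no assignment until the participant has consented and completed baseline.
2. Preferred: the biostatistician releases the whole cohort's assignments in one batch after the last baseline visit. This also removes the predictability of the fixed 6:6 blocks of 12. It fits the schedule, since section 2.9.1 places baseline visits 2–3 weeks before the first session and section 2.8 runs both arms at the same time and on the same days.
3. Lesser option: the biostatistician, or another person with no recruiting role, prepares sealed, sequentially numbered envelopes. The guessing rate of about 64% then remains for anyone who learns past assignments.

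For Cohort 1, report who held the sequence and when they received it.

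The cost is a little biostatistician time and, with batch release, participants learning their arm somewhat later. Eligibility, outcomes, interventions and sample size do not change.
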